# Study Design

A pilot, two-centre, two-arm, parallel group, block randomised (1:1) controlled trial will compare SRT with a SHE control. Both groups will continue to receive standard breast cancer treatment as usual (TAU). Consistent with the requirements of a pragmatic trial, there will be no limitations upon usual care for either group. In this way, the trial represents a comparison of SRT+SHE (+TAU) vs. SHE (+TAU), permitting clear judgements to be made regarding the relative clinical utility of SRT. Due to the nature of the SRT intervention, the therapist and patients cannot be blinded to treatment allocation. However, the statistician will be blinded to treatment allocation (i.e., SRT or SHE) until after analysis is complete.

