The second stage of screening involves the completion of a semi-structured interview (on Qualtircs or administered by the researcher over Zoom/Teams or telephone) to establish full study eligibility. This includes assessment of current sleep status (based on diagnostic criteria for acute insomnia outlined in 6.1 above), current psychiatric symptoms and review of other relevant medical information (diagnosis of other sleep disorders, other medical and psychiatric disorders). This is to confirm the diagnosis of acute insomnia and establish that there are no medical or psychiatric conditions that might preclude someone from taking part in the study. During screening, we will also give each participant the opportunity to sign a health release form. This will give us permission to contact their health care provider of choice (e.g., their GP) with information that has been uncovered as part of their participation in this study (and only this information e.g., uncovering potential Major Depressive Disorder), that might warrant further follow-up but that cannot be provided as part of this trial. This will be an opt-in opportunity, and not signing the health release form will not have any impact on their participation in the study. In cases where the participant discloses suicidal ideation or physical/sexual abuse to them or others, the respective authorities will be contacted by the CI even if consent for this action is not provided by the participant. This is made clear to the participant in the participant information sheet and also verbally prior to screening. Once eligibility is ascertained, patients will be randomly assigned to SRT or the SHE control group.

- 1. Randomisation

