We aim to randomise 40 patients (n=20 in each trial arm), and conservatively estimate that we will recruit 5 patients per month across both sites in a 10-month recruitment window (assuming a dropout rate of 20%). This represents <10% of the total number of patients seen per month in these clinics. NHS Greater Glasgow and Clyde and NHS Grampian serve a combined population of around 1.7M. In the NHS GGC South Sector breast service, based at Gartnavel General Hospital, there are 550 new breast cancers each year, with over 60% of this population undergoing surgery as their primary treatment. In NHS Grampian, 545 new breast cancers (screening and symptomatic pathways) were diagnosed in 2021. About 84% of these newly diagnosed patients received surgery as their primary treatment. Of these, we conservatively estimate that 40% will meet criteria for acute insomnia (n=315). From these, we aim to randomise patients to take part in the study.

- 1. Study Assessment Points

After randomisation to SRT or SHE, patients will be sent an email with a link to complete a baseline (pre-intervention) assessment of sleep, fatigue, and mental health (questionnaires can be completed over the telephone or on paper should the participant prefer this). Patients will also be required to complete the consensus sleep diary and wear an actigraphy device for 7 days prior to commencement of SRT/SHE to record sleep and rest/activity rhythms. Within-treatment session outcomes for SRT will also be explored using sleep diaries and actigraphy. After completion of the baseline assessment, patients will either be referred to the nurse therapist for commencement of the SRT protocol or provided with the SHE resource. At 6 weeks, and 12 weeks post-randomisation, patients will be requested to complete the same battery of questionnaires as during the baseline assessment. Following completion of the final study assessment (12 weeks post-randomisation), those randomised to the SHE condition will be offered the opportunity to complete the SRT protocol without the requirement to complete any further assessments.

- 1. Primary and Secondary Outcomes

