• Session 4 (10 minutes) – The nurse therapist will telephone the patient to check progress, provide an opportunity for questions, and advise on further titration of the patient’s sleep schedule if required. Suggestions for ongoing implementation and the management of residual or recurrent insomnia symptoms will also be provided during this final session.

- 1. Sleep Hygiene Education (SHE)

SHE will be delivered via a booklet that provides information about lifestyle changes (e.g., reducing exercise in the evening, light snack before bedtime, reducing caffeine) and changes to the bedroom environment (e.g., dark room, comfortable mattress, optimal room temperature). Patients in the SHE condition will be instructed to implement the SHE advice over a 4-week period. One week after randomisation to SHE, the RA will telephone patients to check they understand the SHE advice and answer any questions they may have. However, the SRT nurse therapist will have no input into delivery of SHE and will not review patients randomised to this condition. SHE has successfully been used as a control condition in other trials evaluating SRT and does not have any therapeutic benefit for individuals with insomnia but is often part of usual care, so is a credible alternative to SRT.

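### Baseline is collected after randomisation from unblinded patients, so it can be affected by allocation, and the 6-week clock starts before treatment can

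*Protocol*

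**What the plan says.** The order of events is set in the Protocol, Procedures. After the second stage of screening: "Once eligibility is ascertained, patients will be randomly assigned to SRT or the SHE control group". Then, under Study Assessment Points: "After randomisation to SRT or SHE, patients will be sent an email with a link to complete a baseline (pre-intervention) assessment". In the same paragraph patients complete the sleep diary and "wear an actigraphy device for 7 days prior to commencement of SRT/SHE".

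Treatment waits for this: "After completion of the baseline assessment, patients will either be referred to the nurse therapist for commencement of the SRT protocol", or are given the SHE resource. Follow-up does not wait: "At 6 weeks, and 12 weeks post-randomisation, patients will be requested to complete the same battery of questionnaires as during the baseline assessment".

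Table 2 lists ISI, PHQ-9, GAD-7, FACT-F, diary and actigraphy from baseline onward and none of them at screening. Study Design states that "the therapist and patients cannot be blinded to treatment allocation".

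Under Interventions, both SRT and SHE last 4 weeks, and the baseline diary informs the SRT schedule. For the control arm: "One week after randomisation to SHE, the RA will telephone patients to check they understand the SHE advice".

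Data Analysis specifies one efficacy test, a t-test or Mann-Whitney comparison of ISI between arms at 6 weeks, with no baseline term. The secondary outcomes under Procedures are worded as improvements at 6 and 12 weeks.

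**The concern.** A baseline value is useful because allocation cannot have influenced it. Here every baseline outcome is measured after allocation, and all but actigraphy are self-reported. One arm is to receive four sessions with a nurse therapist. The other is to receive a booklet and a telephone call, with SRT offered only after week 12. A patient who knows which she will get may rate her sleep or mood differently. She may also change her time in bed or napping during the diary week, or leave the study without giving any baseline. The diary matters twice, because it is both an outcome and an input to the SRT schedule.

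The second issue is timing. The follow-up clock starts at randomisation, but treatment starts only after at least a week of baseline recording. The 6-week ISI, the only comparison with a power calculation, therefore has limited room after the end of a 4-week course.

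**Working it through.** **1. The plan's own figure.** Inputs from Data Analysis: ISI difference 4.2, SD 4.5, power 80%, significance level 5% (two-sided assumed).
- Standardised difference: 4.2 / 4.5 = 0.933.
- Two-sample t-test: n = 19.03 per arm, rounded up to 20. Power at 20 per arm is 82.0%.
- With 20% dropout: 20 / 0.80 = 25 per arm.

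The stated 20 and 25 reproduce. Nothing below changes them.

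**2. Is there any pre-randomisation outcome value?** Procedures goes from eligibility straight to allocation and sends the baseline questionnaires afterwards. Table 2 has no outcome measure at screening. So there is none.

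**3. Which analyses a shifted baseline would reach.** Suppose knowledge of allocation moves mean baseline ISI by b points in one arm relative to the other.
- Unadjusted 6-week contrast: baseline does not enter, so the error is 0.
- Change-score contrast: the error is b.
- Baseline-adjusted contrast: the error is about ρ × b, where ρ is the baseline to follow-up correlation (equal variances assumed).

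The documents give neither b nor ρ. Both are assumed below, and the direction is unknown.

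| Assumed b (ISI points) | 6-week contrast | Change score | Adjusted, ρ = 0.3 | Adjusted, ρ = 0.5 | Adjusted, ρ = 0.7 |
|---|---|---|---|---|---|
| 0.5 | 0 | 0.5 | 0.15 | 0.25 | 0.35 |
| 1 | 0 | 1 | 0.3 | 0.5 | 0.7 |
| 2 | 0 | 2 | 0.6 | 1.0 | 1.4 |

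**4. Timing.** Randomisation is day 0, the 6-week assessment is day 42, and the course lasts 28 days in either arm. Baseline takes at least 7 days, so the earliest start is about day 7. End of course = start + 28, and margin = 42 − end. Starts after day 7 are assumed.

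| Start day | End of course | Margin to day 42 | Days from start to day 42 |
|---|---|---|---|
| 7 (earliest) | 35 | 7 | 35 |
| 10 | 38 | 4 | 32 |
| 14 | 42 | 0 | 28 |
| 21 | 49 | −7 | 21 |
| 28 | 56 | −14 | 14 |

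The 6-week ISI falls inside the treatment phase for any start after about day 14. If the 6-week diary covers the seven days ending on day 42 (an assumption), those are days 36 to 42, and a start later than about day 7 already overlaps treatment.

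With baseline completed before randomisation and a prompt start, the course ends near day 28 and the margin is 42 − 28 = 14 days.

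**5. The SHE call.** It is timed at one week after randomisation. The SHE resource is supplied only once a baseline of at least 7 days is complete. The call can therefore fall on or before the day the patient receives the material it is meant to check.

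**The case against.** The strongest reply is that the one specified efficacy test uses only the 6-week ISI, so no shift in baseline can bias it. That stands in full. A reader might infer that the planned comparison is compromised, or express an assumed 1-point shift as a share of the planned 4.2 points. The documents do not support this, because 4.2 belongs to the contrast that is unaffected.

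Other stronger readings also fail:
- **Patients complete baseline knowing their arm.** The Protocol says they cannot be blinded, not when they are told. The SHE call implies knowledge by about one week. Only the weaker statement, that baseline can be affected, is supported.
- **A late start means the 6-week ISI precedes session 4.** Session dates are not fixed. If sessions were weekly (an assumption), session 4 would fall 21 days after session 1, which is day 28 for a day-7 start and 14 days before the assessment. The text supports only that the 4-week phase may be incomplete.
- **The timing problem affects SRT alone.** SHE also starts after baseline and runs for 4 weeks, so a late start shortens exposure in either arm.

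It is also fair to say that the primary outcomes concern feasibility, that early loss is what the attrition criterion is meant to detect, and that 20% dropout is allowed for. On the Protocol's fastest schedule, both courses finish before week 6.

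Finally, randomising only patients with complete baseline questionnaires would make baseline completion 100% among those randomised, and so distort the 70% completion criterion in Table 1. This is a valid limit on how the order is changed, and the fix below allows for it. None of these replies supplies a baseline free of allocation or removes the conflict over the SHE call.

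**Conclusion.** The point holds as a design weakness that should be fixed, not as an error in the main comparison. No outcome is measured before allocation. What can be biased are the improvements named as secondary outcomes, any baseline-adjusted analysis, the baseline comparison of the arms, and the diary used for the SRT schedule. Patients who disengage on learning their arm would contribute no baseline.

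The size cannot be derived from the documents. Under an assumed between-arm shift of 0.5 to 2 ISI points, change-score contrasts move by 0.5 to 2 points. Baseline-adjusted contrasts move by 0.15 to 1.4 points for correlations of 0.3 to 0.7.

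The timing conclusion rests only on the stated durations: at most about 7 days between the end of a 4-week course and the 6-week assessment, and none if treatment in either arm starts at day 14 or later. The sample size is unaffected.

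**What to change.** - **Reorder the procedures:** consent, eligibility, baseline questionnaires with the 7-day diary and actigraphy, then randomisation, then a prompt start of the intervention. Keep 6 and 12 weeks counted from randomisation.
- **Protect the feasibility criteria:** report losses between consent and randomisation. Calculate baseline questionnaire completion among all consented eligible patients, so that the 70% criterion is not met by construction.
- **Reconcile the SHE passages:** the one-week call (Interventions) and the time at which the SHE resource is supplied (Procedures) must be made consistent.

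This adds no assessment and leaves the sample size unchanged. It delays allocation by about a week, within the limited window before chemotherapy or radiotherapy, and some patients will be lost before randomisation. The change helps only patients not yet randomised, since a pre-allocation baseline cannot be recovered afterwards.

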Sleep Restriction Therapy (SRT) is an established, single-component treatment for ID and a key ingredient within multicomponent Cognitive Behavioural Therapy for insomnia (CBT-I) ([12](#_ENREF_12)). SRT targets altered rest/activity rhythms, with the aim of increasing homeostatic sleep pressure, over-riding cognitive and physiological arousal, and strengthening circadian control of sleep ([12](#_ENREF_12)). This is because sleep extension leads to a disparity between sleep opportunity and sleep ability, alters the regularity of the sleep-wake schedule, and consequently, increases exposure to light, the chief zeitgeber for the circadian clock. Therefore, whilst SRT may be particularly useful for breast cancer patients with acute insomnia, there are no efficacy studies of SRT in the breast cancer patient population or the acute insomnia population.

One of the strengths of our approach is that it identifies patients with initial sleep disturbance who would benefit from early intervention to prevent insomnia progression. However, robust research is required to evaluate whether SRT is tolerable for newly diagnosed breast cancer patients at such a challenging time. Typically, cancer patients undergoing active treatment are excluded from sleep research studies, so their ability to commit during a time of high psychological impact is unclear. Reassuringly, our Public and Patient Involvement (PPI) group strongly endorse our research plans, and the importance of offering SRT during the acute cancer treatment phase, not least because of the potential for prevention of ID. Finally, assessing intervention acceptability will provide insight into potential optimisation of SRT and recommendations for enhancing future scalability and translation within healthcare. This study will identify and resolve these key areas of uncertainty, informing the design of a larger randomised controlled trial (RCT) and minimise barriers to wider-scale adoption of SRT within cancer care settings.

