6. *Consensus Sleep Diary:* Prospective daily diary entries will be used to assess self-reported sleep patterns over a 7-day period. Sleep diaries are a reliable and valid index of insomnia and have been used as an outcome measure in efficacy studies on insomnia. During the baseline, intervention, 6 week and 12 week assessment, prospective self-report data will be collected using the consensus sleep diary. This consists of an assessment of bedtime, sleep onset latency, wake time after sleep onset, rise time, total sleep time, ratings of sleep quality and napping behaviour.
7. *Actigraphy:* The actigraphy device is a wristwatch like device that measures activity through an accelerometer (motion sensor that records the occurrence and degree of motion). Reduced activity can be used as a proxy for sleep, thus providing information about the sleep-wake cycle.
8. *The Client Service Receipt Inventory (CSRI):* The CSRI is a research tool that collects information on service utilisation, income, accommodation and other cost-related variables.
9. *Patient Satisfaction with Treatment:* An adapted version of the Patient Satisfaction Questionnaire Short Form (PSQSF) will be used to assess patient’s treatment satisfaction with the intervention.
10. *Safety:* Adverse events unrelated and related to the interventions will be recorded during treatment. A side-effects inventory, which was developed for individuals with insomnia undergoing behavioural treatments, will be used. Serious adverse events such as deaths, suicide attempts, and serious accidents will also be recorded. We will also encourage patients to contact us with any changes to their health and wellbeing.

Table 2: Overview of scheduled study assessments

| **Measures** | **Screening** | **Baseline (T0)** | **During SRT** | **6 weeks post-randomisation** | **12 weeks post-randomisation** |
| --- | --- | --- | --- | --- | --- |
| ISI, PHQ-9, GAD-7, FACT-F, |  | X |  | X | X |
| Sleep diary |  | 7 days | Daily | 7 days | 7 days |
| Actigraphy |  | 7 days |  | 7 days | 7 days |
| Enrolment logs (recruitment) | X |  |  |  |  |
| Fidelity rating scale (therapist adherence) |  |  |  | X |  |
| Intervention attendance logs (patient engagement) |  |  | X |  |  |
| Client Service Receipt Inventory (control group contamination) |  |  |  | X | X |
| Adverse Events |  |  | X | X | X |
| Treatment Satisfaction |  |  |  | X |  |
| Exit interviews (intervention acceptability) |  |  |  | X |  |

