# Adverse Event Ascertainment and Reporting

12.1 Definitions of Adverse Events, Serious Adverse Events, and Unanticipated Problems

Adverse events (AEs) will be defined as any unwanted medical event, reaction or side effect that occurs during the research study. Any relationship to study procedures will be determined and each AE defined as either unrelated or possibly, probably, or definitely related to participation in the study. The severity of the AEs will be determined by the type and outcome of the AE. Serious AEs (SAEs) are classified as such if the event results in death, disability, hospitalisation, deformation, congenital abnormality birth defects or any medical events that might lead to the outcomes listed above. The classification of the AE is determined irrespective of the relationship to the study interventions. An adverse event will be classified as an unanticipated problem (UP), if the AE is unexpected, if it is related or possibly related to the study procedures, and if the occurrence indicates that the participants or others are placed at greater risk by completing the study that previously assumed.

12.2 Unsolicited/Solicited Assessment and Reporting of Adverse Events and Unanticipated Problems:

AEs will be assessed systematically using a side effects inventory. Patients will also be encouraged to disclose any AEs, new symptoms or major life events during each assessment (unprompted side effects assessment). Additionally, sleep diaries and self-report questionnaires will be reviewed for any emerging symptoms. All AEs will be recorded in an adverse event reporting form, where a detailed description of the event and follow-up action will be recorded. Additionally, the form will provide an opportunity to record whether the event is classified as serious, whether it is related to the study procedures, and whether it is an unexpected AE (see definitions above). The adverse event form will be passed to the CI for review. All SAEs will be reported to the Ethics Committee within 48hrs and UPs that do not meet criteria for SAEs will be reported to the CI within 48hrs, who is responsible to reporting to the Ethics Committee within 30 days. All remaining AEs will be collated for the steering group committee.

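### Table 2 schedules treatment-phase adverse-event collection only under SRT, so events in those weeks are likely to be found more completely in that arm

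*Protocol*

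**What the plan says.** **Text.** Under Assessment Tools, the safety item states: "Adverse events unrelated and related to the interventions will be recorded during treatment". It adds: "We will also encourage patients to contact us with any changes to their health and wellbeing". Section 12.2 says "AEs will be assessed systematically using a side effects inventory", that "Patients will also be encouraged to disclose any AEs, new symptoms or major life events during each assessment (unprompted side effects assessment"), and then: "Additionally, sleep diaries and self-report questionnaires will be reviewed for any emerging symptoms". None of these sentences names an arm, and none gives the inventory a recall period.

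**Table 2.** The row reads "Adverse Events | | | X | X | X". The three marks fall in the columns for the SRT phase, 6 weeks and 12 weeks. There is no treatment-phase column for SHE or for both arms together.

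**Contacts.** Under Interventions, SRT consists of two online sessions and two telephone calls over 4 weeks. SHE is a booklet to be followed for 4 weeks, with one call: "One week after randomisation to SHE, the RA will telephone patients to check they understand the SHE advice". The nurse therapist does not review SHE patients.

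**Purpose.** The Background states that "robust research is required to evaluate whether SRT is tolerable for newly diagnosed breast cancer patients at such a challenging time". Preparatory Research also describes tolerability during cancer treatment as unclear.

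**The concern.** If sites follow Table 2, SRT patients have an adverse-event assessment while they are being treated and SHE patients do not. The weeks in question are those in which short-lived effects such as daytime sleepiness would appear. They may also contain symptoms from the cancer and its treatment, which both arms share. The control arm is what allows those shared symptoms to be separated from effects of SRT.

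With unequal opportunity to detect events, SRT may look less well tolerated than it is when the decision on a full trial is taken. The reverse error is also possible: a real excess under SRT could be put down to closer observation. An analysis plan cannot repair this afterwards, because events that were never asked about in one arm cannot be recovered.

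**Working it through.** The protocol gives no figure on this point to reproduce. The check sets the two arms' schedules side by side, then works out what the timing implies, then illustrates the size.

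**1. Opportunity to detect an event (Table 2; Interventions)**

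| | SRT | SHE |
|---|---|---|
| Intervention period | 4 weeks | 4 weeks |
| Adverse-event columns in Table 2 | 3 (treatment, 6 and 12 weeks) | 2 (6 and 12 weeks) |
| Scheduled contacts | 4 sessions: 30 + 15 + 20 + 10 = 75 minutes | 1 call, no stated safety purpose |
| Diary between baseline and 6 weeks | daily, about 4 × 7 = 28 entries | none |

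**2. Is the column heading only loose labelling?** The other entries in that column are the daily diary and the attendance logs. Table 1 ties the logs to SRT sessions, and Study Assessment Points describes within-treatment diary outcomes for SRT. The column therefore reads as specific to SRT.

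**3. Does the text fill the gap for SHE?** Section 12.2 invites disclosure at each assessment. For SHE patients, Study Assessment Points lists assessments at baseline, 6 weeks and 12 weeks only. So the text names no arm but gives SHE no treatment-phase assessment.

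**4. Timing of the SHE call.** Count days from randomisation. The 7-day baseline recording follows randomisation and comes before the intervention, so SHE starts on about day 7 at the earliest. The call, one week after randomisation, is also on about day 7. It therefore falls at about the start of SHE. With that earliest start, SHE runs to day 7 + 28 = 35, and the 6-week assessment is on day 42. An event on the first day of SHE would be asked about 42 − 7 = 35 days later.

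**5. Illustration of size. All inputs are assumptions; none is in the documents.** Let the true proportion with an event in the treatment weeks be t = 0.30 in both arms, p the share detected by asking during treatment (0.6 to 0.8), and r the share recalled at 6 weeks (0.4 to 0.7).

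- SRT recorded = t × [1 − (1 − p)(1 − r)]
- SHE recorded = t × r, if nothing is picked up during treatment

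| p | r | SRT | SHE | Ratio |
|---|---|---|---|---|
| 0.6 | 0.4 | 0.30 × 0.76 = 22.8% | 12.0% | 1.90 |
| 0.6 | 0.7 | 0.30 × 0.88 = 26.4% | 21.0% | 1.26 |
| 0.8 | 0.4 | 0.30 × 0.88 = 26.4% | 12.0% | 2.20 |
| 0.8 | 0.7 | 0.30 × 0.94 = 28.2% | 21.0% | 1.34 |

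The ratio does not depend on t. With 25 patients per arm, the gap is between 25 × (0.264 − 0.210) = 1.35 and 25 × (0.264 − 0.120) = 3.6 patients. The SHE formula is the worst case for SHE, since it sets spontaneous reporting to zero. If SHE patients reported as completely during treatment as SRT patients do when asked, the two formulas would be the same and the ratio would be 1.0.

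**The case against.** **The text covers both arms.** A reader might infer from Table 2 that events are collected in the SRT arm only. The documents do not say so. The safety item speaks of the interventions in the plural, section 12.2 speaks of patients generally, and anyone may report at any time. This stands: what can be shown is a conflict between table and text and an unequal schedule, not a rule that excludes SHE.

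**SHE does give a background rate.** A reader might infer that there is none for the treatment weeks. That is too strong. SHE patients have adverse-event assessments at 6 and 12 weeks, complete the FACT-F fatigue scale on the same schedule as SRT patients, and record napping in the 7-day diaries. What remains is that short-lived events in the treatment weeks are captured by recall or by unprompted report, which is less complete.

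**The stopping rule is hardly touched.** The rule under Criteria for Intervention Discontinuation counts study-related serious events, such as death or hospitalisation. These depend little on when an inventory is given. This stands.

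**No between-arm comparison of adverse events is specified.** They are not among the primary or secondary outcomes or the success criteria, and how they are summarised may be left to an analysis plan. This limits the point but does not remove it: tolerability is a stated uncertainty, the trial has a control arm, and the collection schedule is set in the protocol.

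**The diary is a weak source.** Its listed fields cover sleep timing, quality and napping, with no adverse-event item, so 28 entries are not 28 safety enquiries. This stands in part, because section 12.2 does use diaries to look for emerging symptoms.

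**Conclusion.** The point holds as an inconsistency with a likely consequence. Table 2 schedules treatment-phase adverse-event collection under SRT, the text names no arm, and SHE patients have no scheduled adverse-event assessment before 6 weeks. Together with four therapist contacts and reviewed daily diaries in one arm, this makes fuller detection under SRT likely in the treatment weeks, and a between-arm tolerability summary may be biased against SRT.

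The size cannot be derived from the documents. The illustrated ratios of 1.0 to 2.2 rest on assumed detection and recall shares, with the upper end requiring no spontaneous reporting at all by SHE patients. The conclusion would fall away if both arms in practice received the same inventory at the same treatment weeks, but the protocol does not provide for that as written.

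**What to change.** 1. Reconcile Table 2 with the safety item and section 12.2. Relabel the adverse-event column as the treatment period in both arms, and keep the daily diary and attendance logs marked as SRT only.
2. Give the same side-effects inventory, with the same stated recall window, at the same weeks after the start of the intervention in both arms. SHE patients can complete it by online link. The week-1 call should not be used for this, because it falls at about the start of SHE.
3. Base between-arm safety summaries on these common time points. List separately any event found only through an SRT session or a daily diary.

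**Cost.** One changed column in Table 2, a sentence in section 12.2, and a few online inventories for about 20-25 SHE patients. If the inventory were given weekly for the 4 weeks, that would be 4 × 20 = 80 to 4 × 25 = 100 short forms in the whole SHE arm. The downside is slightly more questionnaire burden for those patients. The change has to be made before data collection.
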